# The biobehavioral Women’s Health CoOp in Pretoria, South Africa: study protocol for a cluster-randomized design

**DOI:** 10.1186/1471-2458-14-1074

**Published:** 2014-10-15

**Keywords:** Vulnerable women, HIV, South Africa, Combined biobehavioral intervention, Women’s Health CoOp, Seek, test, treat and retain paradigm, Cluster-randomized design

## Abstract

**Background:**

South Africa has 6.4 million adults over the age of 15 living with HIV. Gender inequality issues continue to drive the HIV epidemic in South Africa, where Black African women bear the greatest HIV burden. Limited access to services; little capacity to negotiate sex and condom use; and other legal, social, and economic inequities make women highly vulnerable to HIV infection. Behavioral interventions have been shown to decrease risk behaviors, but they have been less successful in reducing HIV incidence. Conversely, biomedical prevention strategies have proven to be successful in reducing HIV incidence, but require behavioral interventions to increase uptake and adherence. Consequently, there is a need for integrated approaches that combine biomedical and behavioral interventions. Effective combination prevention efforts should comprise biomedical, behavioral, and structural programming proven in randomized trials that focuses on the driving forces and key populations at higher risk of HIV infection and transmission.

**Methods/Design:**

This prospective, geographically clustered randomized field experiment is enrolling participants into two arms: a control arm that receives standard HIV testing and referral for treatment; and an intervention arm that receives an evidence-based, woman-focused behavioral intervention that emphasizes risk reduction and retention, the Women’s Health CoOp. We divided the city of Pretoria into 14 mutually exclusive geographic zones and randomized these zones into either the control arm or the intervention arm. Outreach workers are recruiting drug-using women from each zone. At baseline, eligible participants complete a questionnaire and biological testing for HIV, recent drug use, and pregnancy. Follow-up interviews are completed at 6 and 12 months.

**Discussion:**

The biobehavioral intervention in this study merges an efficacious behavioral HIV prevention intervention for women with biomedical prevention through HIV treatment as prevention using a Seek, Test, Treat and Retain strategy. This combination biobehavioral intervention is designed to (1) improve the quality of life and reduce HIV infectiousness among women who are HIV positive, and (2) reduce HIV risk behaviors among women regardless of their HIV status. If efficacious, this intervention could help control the HIV epidemic in South Africa.

**Trial registration:**

Trial registration no: NCT01497405.

## Background

South Africa has the highest number of people living with HIV in the world. HIV prevalence increased in South Africa from 10.6% in 2008 to 12.2% in 2012 [1]. This increase likely reflects more accurate estimates arising from the widespread testing campaigns and a reduction in HIV-related mortality as a result of the large-scale expansion of antiretroviral therapy (ART) programs [2] coupled with continued HIV incidence. Although the epidemic is generalized, a number of concentrated subepidemics exist among specific groups that have HIV prevalence above the national average [3], including young Black African women and high-risk alcohol and recreational drug users. A survey by the South African Human Science Research Council (HSRC) reported that although the epidemic has stabilized, Black African women are still the most affected. HIV prevalence among Black African women aged 15 to 49 is 23.2%, whereas prevalence among their male counterparts is 18.8% [4]. The HSRC survey also found that among adults aged 15 to 49, the number of new infections was 1.7 times as high among females as among males. Moreover, among females aged 15 to 24 the HIV incidence rate was over four times higher than among males in this same age group.

Although 37% of men and women between the ages of 15 and 49 have been tested for HIV, testing rates are much lower among key populations, such as female sex workers or women who use alcohol or other drugs (AOD). This is problematic because HIV prevalence among female sex workers exceeds 50% in some areas [5], 65% in South Africa, and HIV prevalence among women who use AOD but are not sex workers is often greater than 30% [6]. Despite the high prevalence of HIV, only 60% of female sex workers are reached by current HIV prevention programs (e.g., HIV testing, condom distribution) [7]. This relatively low rate of HIV testing in this key population represents a missed public health opportunity [8].

Economically disadvantaged women, many of whom use AOD, are often responsible for supporting themselves and their extended families. Under these circumstances, they may resort to sex work and engage in high rates of unprotected sex with multiple partners [9]. A majority of these partners also have concurrent partnerships, which further contributes to the spread of HIV in South Africa [10]. A study in Ghana found that 84% of HIV infections among males aged 15 to 59 could be attributed to transactional sex [11]. In simulation models, the presence of sex workers led to a substantially larger heterosexual HIV epidemic. Taken together, the findings from the epidemiological and modeling studies suggest that interventions to reduce risk for sex workers could slow the epidemic [12].

Biomedical interventions, such as increasing the percentage of people living with HIV that receive ART, have been associated with reducing HIV transmission [13]. One meta-analysis of 11 cohort studies of discordant couples estimated that ART in the index case resulted in a 92% reduction in HIV incidence [14]. Other studies that examined the effect of HIV treatment at the community level reported associations between reductions in community viral load and reductions in HIV incidence [15, 16]. These findings suggest that widespread use of ART can reduce HIV transmission at the community level.

ART and other biomedical interventions require adherence to the medications to be effective. Without adherence, HIV antiretroviral (ARV) resistance mutations can occur, leading to loss of viral suppression with risk to the patients and their sexual partners. Substance abuse is a critical barrier to ART adherence [17]. Widespread access to ART may lead to riskcompensation, i.e., an increase in risky behavior caused by actual or perceived lower risk. Risk compensation occurs when people feel that they are no longer at risk of HIV infection or transmission [18]. The combined effect of incomplete viral suppression and risk compensation could potentially further increase transmission to partners. Consequently, it is important for biomedical HIV interventions to continue to emphasize behavioral prevention, particularly condom use even after initiating ART [19].

While biomedical intervention strategies reduce the probability of HIV acquisition and transmission, behavioral interventions promote reductions in risk behaviors, adherence to medications and clinic visits, and condom use; however, few are specifically gender interventions focused on women’s issues. In addition, there is growing recognition that combination interventions with biomedical and evidence-based behavioral strategies coupled with structural change components—such as increased access to ART and substance abuse treatment—are more effective in reducing HIV transmission than any of these strategies alone [20–22]. Prevention packages that combine effective woman-focused interventions should be implemented and scaled up to achieve a measurable reduction in population-level HIV prevention [23].

## Methods/Design

### Objectives

The aim of this study is to assess the relative impact of adding the Women’s Health CoOp (WHC) to standard Test, Treat, and Retain (TTR) practices on the numbers of HIV-positive, AOD-using women who receive medical evaluations (e.g., CD4, viral load), initiate treatment, remain in treatment, and have suppressed viral load. It will also assess the relative impact of adding the WHC to TTR practices on reductions in risk behaviors (e.g., AOD use, not using condoms, victimization) among all women, regardless of their HIV status.

### Study design

This study is a prospective, geographically clustered randomized two-group field experiment. It is being conducted in 14 geographic clusters in Pretoria, South Africa (Figure 1). We chose the cluster randomized design to minimize contamination between study arms. The study will assess the efficacy of a combined HIV/AIDS prevention/intervention and enhanced strategy targeting AOD-using women for ART initiation, adherence, retention, and reduced risk behaviors compared with standard TTR practices in South Africa. Recruitment started in 2012 and will end in 2014. Follow-up interviews conducted at 6 and 12 months post-enrollment will continue through 2015.

**Figure 1 Fig1:**
[figure not shown]
**Anticipated recruitment, intervention participation, follow-up, and allocation of clusters.**

### Setting

We divided the entire city of Pretoria—which includes a central business district, other commercial areas, and residential areas such as a number of formal and informal townships and settlements—into 14 mutually exclusive “zones.” We delineated the zones according to natural boundaries based on consultation with outreach workers who were knowledgeable about Pretoria.

### Randomization

We created seven pairs of zones that were matched on the basis of socioeconomic conditions and estimates of the number of sex workers and women who use AOD residing in them. These estimates were based on inputs from our outreach workers who had worked on one of our prior studies that reached drug-using, at-risk women and sex workers in the Pretoria area [23–25].

We randomized zones within each pair to the control arm or the intervention arm. Each participant’s study arm is determined by the zone in which she was recruited.

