#### Outcome measures

The primary outcome is self-reported male or female condom use during the participant’s most recent episode of vaginal or anal intercourse. Other outcomes include frequency of condom use, frequency and quantity of alcohol use, urine drug screen results for illicit substance use, and frequency of violent victimization (physical or sexual). Additional outcomes for women living with HIV include receiving HIV treatment, ART adherence, and CD4 counts. Analyses for HIV-RNA viral load on stored dried blood spots at follow-up may occur at a later date.

Alcohol use is measured biologically with a breathalyzer test and through self-report. A biological urine drug screening test determines recent use of a panel of substances, including cannabis/marijuana, opioids, cocaine, methamphetamine, and Mandrax (methaqualone). Victimization includes self-report of being beaten, attacked with a weapon, or forced to have sex during the previous 90 days. We assess if women living with HIV received treatment and took ART both biologically and by self-report. Self-report for ART refers to being prescribed ART, taking ART if prescribed, and missing any doses in the past 30 days. We also examine measures of adherence included in the U.S. National Institute on Drug Abuse’s harmonization initiative [30]. To help interpret these data, we also collect self-reports of barriers to ART use.

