#### Sample size and power

The sample size was lowered to 600 from 1050 as originally planned. The original sample size was calculated on the basis of an anticipated HIV prevalence of 30%; however, HIV prevalence in the sample is 55%. Accordingly, the smaller sample (n = 600) will allow for the identification of a clinically meaningful effect with sufficient statistical power, while accounting for logistical difficulties, including a citywide study, limited structural resources, increased costs, and other factors outside the control of the study. We assume 14 clusters, approximately 30 observations per cluster and 20% attrition, yielding a final sample size of about 480 respondents at 12-month follow-up. This allows us a medium to strong likelihood of detecting an effect of the intervention assuming a strong effect (based on Cohen’s beta of 0.6). This would translate to an approximately 10% to 15% difference in the outcomes for any behavioral outcome (e.g., reductions in AOD use, number of instances of unprotected sex). We would not be able to detect mild to weak effects in analyses that consider the mediation of the effect of the intervention through some cognitive outcome, such as intentions/self-efficacy/knowledge/gender power. The reduction in power also greatly reduces the likelihood of testing whether the intervention yielded modification effects across the levels of some covariate and mediational effects as well. However, we will examine the distribution of the variables and reestimate power given the final sample size and variance estimates. No outcome or mediator/moderator analyses will be conducted unless there is strong power (e.g., Beta greater than .8, for a 2-tailed test and p = .05).

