#### Analysis

We will first conduct descriptive statistical analysis of baseline variables and clinical characteristics of the two intervention arms to examine the extent, if any, of baseline or clinical imbalances between the two arms using contingency table analyses (Mantel-Haenszel for categorical and analysis of variance for continuous variables). The analysis will center around estimating the impact of the intervention on each of the primary study outcomes, observed at baseline and 6- and 12-month follow-up visits, using all available cases consistent with an intent-to-treat method. In addition to evaluating changes in each outcome by intervention arm at 6-month follow-up, the analysis will examine whether the changes are sustained or decay at 12-month follow-up. Given the longitudinal nature of the data, our primary analytic strategy will apply a generalized estimating equation (GEE) modeling approach to account for the multiple dependencies of repeated measures collected on the same individuals over time, and the clustering of the outcomes by community. Because the communities may range from 5 to 100 cases, the generalized linear/nonlinear mixed model (e.g., hierarchical linear modeling or multilevel modeling with random effects) would likely face problems with convergence given the heterogeneity in the variation between communities. Therefore, we opt for a statistical strategy that treats this level of clustering as a nuisance parameter, and thereby estimating the population-averaged effects of the outcomes for subjects sharing the same profile of individual and community-level characteristics. For outcomes with binomial or count distributions, the logit link will be specified to obtain effect estimates of the magnitude of differences between arms within each follow-up visit. For continuously distributed outcomes, an identity link function will be specified. We expect that we will estimate the working correlation matrix at the temporal level using a first-order autoregressive structure (AR-1) and an exchangeable correlation matrix at the community-level, thereby allowing the subjects within each cluster to be constrained to equality but freeing the estimates between clusters.

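### The primary GEE leaves out the seven matched pairs used for randomisation, and it describes two contrasts, of which the one tied to the model leaves baseline imbalance in the effect

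*Protocol article*

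**What the plan says.** **Design.** The Randomization section says "We created seven pairs of zones that were matched on the basis of socioeconomic conditions", and on outreach workers' estimates of how many sex workers and AOD-using women live in each zone. Then: "We randomized zones within each pair to the control arm or the intervention arm". Each woman's "study arm is determined by the zone in which she was recruited". The pair is therefore the randomisation block, and women enter after their zone has been allocated.

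**Outcome.** "The primary outcome is self-reported male or female condom use during the participant’s most recent episode of vaginal or anal intercourse".

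**Analysis.** The Analysis section names two dependencies for the GEE: repeated measures on the same woman and clustering by community. It gives a link function, an AR-1 structure over time and an exchangeable structure by community. Pair is not a stratum, a covariate or a correlation level.

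**Contrast.** The same section includes baseline among the analysed visits and says that change by arm at 6 months will be evaluated. For binary outcomes it then specifies the logit link "to obtain effect estimates of the magnitude of differences between arms within each follow-up visit". It does not say whether that difference is net of baseline.

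**The concern.** An analysis should follow the randomisation. If matching made the two zones of a pair alike, an analysis that ignores pairs counts between-pair variation as error. Its intervals are then too wide and its test rejects too seldom. With only seven zones per arm and a stated target of 10 to 15 points, that loss matters.

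The two contrasts are different estimands. If condom use already differs between arms at baseline, the change contrast removes the difference and the follow-up contrast keeps it. With few zones, and recruitment after zone allocation, such a difference is plausible. If the wording stays open, the choice of contrast, and of keeping or breaking the matching, could be made after the results are known.

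**Working it through.** **Inputs from the protocol article.** 14 zones in 7 pairs; 600 women; 20% attrition; zones of 5 to 100 women; two-sided test at 0.05; and, on effect size, "This would translate to an approximately 10% to 15% difference in the outcomes for any behavioral outcome".

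**Inputs the article does not give, so assumed.** Outcome proportion p = 0.5; ICC 0.02 to 0.05; within-pair correlation of zone effects (rho) 0 to 0.8.

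**1. The plan's own figure.** It states "approximately 30 observations per cluster and 20% attrition, yielding a final sample size of about 480 respondents at 12-month follow-up". 600 × (1 − 0.20) = 480 reproduces. (14 × 30 = 420 does not, so m = 480/14 = 34.3 per zone is used below.)

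**2. Standard error with and without pairs.** Between-zone variance is Vc = ICC × p(1 − p). Within-zone variance of a zone mean is Vw = (1 − ICC) × p(1 − p)/m.

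- SE ignoring pairs = √[2(Vc + Vw)/7], 12 df
- SE respecting pairs = √[2(Vc(1 − rho) + Vw)/7], 6 df

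Example, ICC 0.05 and rho 0.8: Vc = 0.0125 and Vw = 0.95 × 0.25/34.3 = 0.0069. Ignoring pairs, √(2 × 0.0194/7) = 0.0745. Respecting them, √(2 × 0.0094/7) = 0.0519. The ratio is 1.43. Both variances scale with p(1 − p), so the ratio does not depend on p.

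| ICC | rho | SE too large by | 95% half-width, unmatched / paired |
|---|---|---|---|
| 0.02 | 0 | 1.00 | 0.128 / 0.144 |
| 0.02 | 0.5 | 1.12 | 0.128 / 0.128 |
| 0.02 | 0.8 | 1.22 | 0.128 / 0.118 |
| 0.05 | 0 | 1.00 | 0.162 / 0.182 |
| 0.05 | 0.5 | 1.21 | 0.162 / 0.150 |
| 0.05 | 0.8 | 1.43 | 0.162 / 0.127 |

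**3. Simulation.** 4,000 trials per cell, 14 unequal zones, total about 480, power for a 15-point difference.

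| ICC | rho | Type I error: unmatched t / paired t / uncorrected robust z | Power: unmatched t / paired t |
|---|---|---|---|
| 0.02 | 0 | 5.4% / 5.0% / 11.5% | 0.55 / 0.48 |
| 0.02 | 0.5 | 3.2% / 4.2% / 8.8% | 0.55 / 0.53 |
| 0.02 | 0.8 | 2.7% / 4.1% / 6.7% | 0.55 / 0.60 |
| 0.05 | 0 | 4.3% / 4.2% / 10.8% | 0.40 / 0.35 |
| 0.05 | 0.5 | 2.3% / 4.3% / 7.1% | 0.39 / 0.46 |
| 0.05 | 0.8 | 1.4% / 5.1% / 5.0% | 0.39 / 0.54 |

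The excess in the z column comes from few, unequal zones. It is present at rho 0, where pairs play no part.

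**4. The two contrasts.** 200 GEE simulations with no true effect and a lasting baseline advantage for one arm. The arm-by-visit (change) contrast averaged 0.01 log-odds. The arm difference at 12 months averaged 0.34, which near 50% is about 0.34 × 0.25 = 0.085, or 8.5 points. The size of the imbalance was an input; the result shows which contrast carries it.

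**5. Choice of baseline handling.** With follow-up correlation r, the linear-scale variances are proportional to 1 (raw follow-up difference), 2(1 − r) (change) and 1 − r² (baseline-adjusted). At r = 0.3 these are 1, 1.40 and 0.91. At r = 0.7 they are 1, 0.60 and 0.51. Adjustment is never worse than either.

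**6. Permutation within pairs.** 2⁷ = 128 allocations, so the smallest two-sided p is 2/128 = 0.016.

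**The case against.** **Baseline is in the analysis.** This stands. A reader might infer that baseline condom use is collected and then not used. The text does not support that: baseline is one of the repeated outcomes, and change by arm is to be evaluated. What remains is that two contrasts are described, and the one attached to the model does not remove imbalance. Chance imbalance is also covered by a valid zone-level standard error, so for chance alone the loss is precision, not bias.

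**Leaving out pairs does not create false positives.** This stands too. A reader might infer that the error bars are wrong in a dangerous direction. Omitting pairs is harmless if matching failed and conservative if it worked. Nor can the analysis as written be called conservative overall: the low error rates belong to a small-sample reference distribution, which the article does not state, and an uncorrected z-test errs the other way.

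**With seven pairs, breaking the matching is defensible.** Largely true. Moving from 12 to 6 df costs power when matching is weak, and at ICC 0.02 the paired test gains only at rho 0.8. The matching rests on outreach workers' estimates, and that it predicts condom use is an assumption. This is a reason to state the choice in advance, not to leave it open.

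**A journal article may leave this to a fuller document.** Partly. A covariate list may well be elsewhere. But the article does set out the dependence structure of its primary model and omits the level that its own randomisation created.

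**Conclusion.** The point holds in this form: the stated primary GEE ignores the seven matched pairs, and the Analysis section gives two contrasts that differ in whether baseline imbalance is removed.

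On the assumed values, the standard error is too large by 1.0 to about 1.4. At ICC 0.05 this is the difference between a half-width of 0.162 and one of 0.127 to 0.150 if matching is informative (rho 0.5 to 0.8), and a paired analysis is wider (0.182) if it is not. The 5% to 11% type I error of an uncorrected robust z-test is a separate few-zones problem, which inference over within-pair allocations would also address. How much baseline imbalance would enter the effect cannot be fixed from the article, because it depends on an imbalance and a baseline-to-follow-up correlation that are not given.

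The change should be made. It is a cheap improvement and does not mean that the trial's conclusions would be invalid without it.

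**What to change.** 1. Define one primary effect: the arm difference in condom use at 6 and 12 months, adjusted for each woman's own baseline condom use, instead of a raw follow-up difference or a simple change.
2. State that primary inference respects the paired randomisation, for example a permutation test over the 128 within-pair allocations. Otherwise, justify breaking the matching before outcomes are seen, and name an analysis that holds its size with 14 unequal zones.
3. Report a standardised risk difference next to the odds ratio. On the logit scale, baseline adjustment changes the odds ratio from marginal to conditional, whereas the article aims at population-averaged effects.
4. Do not add the zone's baseline mean as a covariate. It is noisy where a zone may have 5 women, and it costs a degree of freedom among 14 zones.

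Cost: wording only, since baseline condom use is already collected. Pairing loses some power if matching is weak (0.55 to 0.48 at ICC 0.02 and rho 0), and the permutation p-value cannot fall below 0.016.
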